Based on the PRISM (*Performance of Routine Information Systems Management*) framework, for data use intervention to be effective, they should address inputs, processes and outputs or performance of routine health information systems (RHIS) [14]. The PRISM framework defined RHIS performance as better quality data and continuous use of information. RHIS performance is a function of RHIS processes and their technical, behavioral and organizational determinants. Addressing these determinants may lead to improved quality of care, better health outcomes and system performance.

In Tanzania, UNICEF and the Data For Implementation (Data.FI) project, funded by the United States Agency for International Development (USAID), are implementing a data use initiative in the primary health care settings with a goal of improving data use in decision making and planning at different levels, Data.FI providing support at the council level while UNICEF in collaboration with PORALG providing support at the facility level. The interventions are implemented in the two regions of Tanzania namely Dar es Salaam and Dodoma, in which two local government authorities (councils) in each of the region have been recruited in the intervention.

Interventions to address data use in primary health care settings are often complex with multiple components. Complex interventions require extensive stakeholder involvement, longer time frames, and are subject to strong contextual influences [15, 16]. As a result, they pose evaluation design and implementation challenges, necessitating a comprehensive approach to program evaluation and monitoring. Desirable evaluation designs are those that aim at: 1) understanding the implementation processes of the intervention and the moderating factors, specifically describing in detail the adoption, fidelity program reach, beneficiaries/client responsiveness and quality of implementation of key process indicators as well as sustainability indictors 2) Using the implementation outcomes to explain the probable variations of effects observed when measuring the impact of the program.

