To assess the extent of adoption of the data use initiativesTo determine number or proportion of beneficiaries reached by the data use initiativeTo assess the fidelity to data use initiative protocol and SOPsTo assess acceptability of the data use initiative by primary beneficiaries and other stakeholdersTo assess sustainability of the data use initiative in the intervened primary health facilitiesTo determine the implementation challenges and success of the data use initiativesUnderstand the effects of the data use initiative on health system and patient outcomes

To understand the effects of the data use initiative, we will collect data at baseline and end line in order to allow two points measures of the outcome data. In this step, to assess compliance to national and international quality standards, the study team will rely both on the analysis of the routine health information system (at the facility level and district level) and information collected from respondents. Specific research questions include, i) has the quality of primary health facility data improved following implementation of the initiative? ii) What factors have contributed to the observed changes?

Specific objectives:-

Assess the effect/impact of data use initiative on beneficiaries’ capabilities (knowledge, and skills to analyze and interpret data)To evaluate the impact/effect of data use initiative on the quality of data collected in the primary health facilitiesTo determine the impact/effect of the initiative on the use of data for decision making and planningTo evaluate the effect of data use initiative on the performance of primary health facilities in terms of quality of delivered health services (availability drugs, medical supplies and equipment) and client’s satisfaction with the services.

*Study component 1*: *Measuring effects of the data use initiative*. This component aims at establishing the effects of data use initiatives on quality of care and selected health outcomes. To establish and control the counterfactual, data will be collected in the intervention and control councils. This component comprises collection of quantitative and qualitative data at two points (baseline and end line) covering a period of one year.

*Sampling and sample sizes*. This component will collect information from health facility documents , health care workers, and patients. The samples and sample sizes for this quantitative component are as follows

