Facility assessment tool: We will use the star rating tool to understand the baseline situation in relation to quality of care of the health facilities. The star rating tool is a validated instrument that has been used to measure quality of care in the health facilities in Tanzania. We will measure the changes in indicators related health system building block indicators (financing, availability of health commodities, and motivation of human resource for health) that could reflect the effects of data use at health facility level.Patient exit interview questionnaire: We will use a patient exit questionnaire to understand patient’s experiences and perceptions on the quality of care provided in health facilities. These questionnaires are also part of the star rating tool, i.e., we will adopt all the questionnaire in the star rating toolNB: The star rating tool consists of facility assessment and exit interview questions and has been used repeatedly to assess quality of health care services in Tanzania [33]. During the baseline assessment, we will also pilot and validate an organizational readiness tool geared to assess health workers readiness to implement data use interventionsHealth workers questionnaire: We will use a health workers questionnaire to understand the situation in relation to data use and the determinants of data use at the facilityObservation checklist: We will use an observation checklist that aims at getting the reality in relation to data use tools, equipment and practices related to data use at the health facilityFor the health outcomes: we will extract data from DHIS2 for selected indicators using a document review checklist/DHS2 data extraction checklist. The indicators include: Number of health facility deliveries, number of pregnant mothers completed 4th ANC visit, NC Total Pregnant Women (PW) tested, Number of pregnant women who tested positive for HIV (First Test), Proportion of pregnant women on ARV to prevent HIV transmission and Number of Maternal Deaths

*Study component 2*: *Measuring implementation process of the data use initiatives*. This component aims to establish data use initiative implementation processes as well as influencing (moderating) factors. This component will be implemented in the intervention councils to better understand the initiative’s implementation processes, thus unlocking the data use initiative’s black box by better knowing the initiative’s components and contextual impacts.

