	4) To assess acceptability of the data use initiative by primary beneficiaries and other stakeholders	Information on affective attitude, burden, ethicality, intervention coherence, opportunity costs, perceived effectiveness and self-efficacy [ACCEPTABILITY]	Documents, participants (health facility managers, health care workers, district managers/CHMT members) and members of Health facility governing committees	Document review checklist, structured questionnaire, semi structured interview guides for in-depth interview
	5) To determine the extent to which the data use practices become part of the routine health facility practices and maintain its effectiveness	Maintenance/ sustainability	Documents, participants (health facility managers, health care workers, district managers/CHMT members) and members of Health facility governing committees	Document review checklist, structured questionnaire, semi structured interview guides for in-depth interview and FGD
	6) To determine the implementation challenges and success of the data use initiatives	Contextual factors	Documents, participants (health facility managers, health care workers, district managers/CHMT members) and members of Health facility governing committees	Document review checklist, structured questionnaire, Semi structured interview guides for in-depth interview and FGD
Outcome evaluation	1) Assess the effect/impact of data use initiative on beneficiaries’ capabilities (knowledge, and skills to analyse and interpret data)	impact of data use (knowledge, skills)	Documents, participants (health facility managers, health care workers, district managers/CHMT members) and members of Health facility governing committees	Document review checklist, structured questionnaire, Semi structured interview guides for in-depth interview
	2) To evaluate the impact/effect of data use initiative on the quality of data collected in the primary health facilities	impact of data quality (relevance; accuracy; credibility; timeliness; accessibility; interpretability; and coherence)	Documents, participants (health facility managers, health care workers, district managers/ CHMT members) and members of Health facility governing committees	Document review checklist, structured questionnaire, semi structured interview guides for in-depth interview

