### 5. Analytical procedures

Descriptive analysis will be used to summarize data where by continuous data will be summarized using mean and standard deviation (SD) as well as medians and interquartile range. Dichotomous variables will be summarized using frequency and percentage. Chi-square test or fisher exact will be used to evaluate bivariate associations between categorical variables where by t-test will be used to estimate association in numeric variables and ascertain whether there mean different between categories. We will also use regression analysis.

Audio-recordings of in-depth interviews and focus group discussions will be transcribed verbatim in Kiswahili guided by a transcription guideline and translated to English. Transcription and translations will be done by the research team that conducted the respective IDIs. Codes will be grouped into categories, sub-themes and themes. Thematic analysis will be used to analyze qualitative data using ATLAS.ti 8 software. Table 2 provides details on data collection tools, administration, sample size and analytical techniques.

**Table 2 pone.0303552.t002:** Data collection tools, administration, sample size and analytical techniques.

S/N	Data collection tool	Level (s) of administration	Method of administration	Sample size (effects measurement)	Sample size (process evaluation)	Analytical techniques
1	Document review checklist	CHMT and Health facility level	physical and e-records, in ODK	Health facilities (N = 40), Districts (N = 4)	Health facilities (N = 20), Districts (N = 2)	Descriptive statistics on frequency, mean and standard deviation, Cross tabulation to compare performance of the participants
2	Semi structured interview guides for in-depth interview	All levels (national, regional, district, health facility, community representatives)	face to face	Patients, dispensary (N = 32), Patients, health center (N = 32), Health care workers, Dispensary (N = 16), Health care workers Health centers (N = 16),	Health facility governing committee members (N = 80), CHMT members (N = 60), RHMT members (N = 4), implementing partners (N = 4)	Thematic analysis will be used to analyze qualitative data using ATLAS.ti 8 software

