3	Structured questionnaire	Health facility level	Face to face (guided), in ODK	Health care workers (N = 440), exit patients (N = 422)	Health care workers (N = 200)	Descriptive statistics (mean, standard deviation), Cross tabulation to compare groups’ performance Regression analysis for checking statistical significances among and between the participants Paired sample t test for comparing means between the baseline and end-line surveys
4	DHS2 extraction form	Health facility level / District level	electronic records	Health facilities (N = 40), Districts (N = 4)		Descriptive statistics on frequency, mean and standard deviation, Cross tabulation to compare performance of health facilities/ districts, Paired sample t-test for comparing means between the baseline and end-line surveys

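### Five of the six DHIS2 health outcomes are raw counts tested baseline against end line, so a change in recording in the intervention arm can be mistaken for a health effect

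*Protocol article*

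**What the plan says.** In section 4 of the protocol article (study component 1, data collection tools), the health outcomes are extracted from DHIS2. The list opens with "Number of health facility deliveries, number of pregnant mothers completed 4th ANC visit, NC Total Pregnant Women (PW) tested" and continues, up to a final item on maternal mortality, with "Number of pregnant women who tested positive for HIV (First Test), Proportion of pregnant women on ARV to prevent HIV transmission and Number of Maternal". Five of the six are numbers of events; only ARV coverage is a proportion.

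Table 2 in section 5 gives the analysis for the DHIS2 form (row 4): descriptive statistics, then "Cross tabulation to compare performance of health facilities/ districts, Paired sample t-test for comparing means between the baseline and end-line surveys". Regression is listed in row 3, for the structured questionnaire, but not in row 4. The section's general text adds only "We will also use regression analysis", without naming an outcome or a model.

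Better routine data is itself an intended result. The Introduction says: "The PRISM framework defined RHIS performance as better quality data and continuous use of information". Section 1b counts the design of the information system among the technical determinants to be addressed. The effects part of section 4 asks "has the quality of primary health facility data improved following implementation of the initiative" and sets the objective "To evaluate the impact/effect of data use initiative on the quality of data collected in the primary health facilities". Table 1 defines that data-quality outcome to include accuracy, credibility and timeliness.

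**The concern.** The system that the initiative is meant to change is also the source of the health outcomes. If facilities in the intervention councils record and transmit more of what they do, the counts move without any change in care or health. The change is expected where the initiative runs and not in the control councils, so subtracting the control arm's change leaves it in place. The limitations in the Discussion cover missing data, recall bias and unidentified confounders, but not a reporting change caused by the intervention.

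Two further problems follow from using raw counts with this test. First, a baseline v end-line test treats any growth in volume over the year as effect. Second, moving to a between-arm comparison of raw changes would not fully repair this: the same proportional growth produces a larger absolute change in the arm with larger facilities.

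At stake is the reading of the health-outcome part of the study objective. A positive result could not be told apart from the initiative succeeding at better recording.

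**Working it through.** The plan states no sample size, effect size, SD or completeness for the DHIS2 outcomes, so there is no figure of its own to reproduce.

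**1. Type of indicator.** Counts: deliveries, fourth ANC visits, women tested, women HIV-positive, maternal deaths = 5. Proportions: ARV coverage = 1. Total 6.

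**2. Apparent change from recording alone.** Apparent change = (completeness after ÷ completeness before) − 1, with true events constant. The completeness values are assumptions.
- 90% to 95%: 95/90 − 1 = 5.6%
- 85% to 95%: 95/85 − 1 = 11.8%
- 80% to 95%: 95/80 − 1 = 18.8%

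**3. Why the control arm does not remove it.** Take 300 true events a year per facility in both arms (assumed) and 80% completeness at baseline.
- Intervention: 300 × 0.80 = 240, then 300 × 0.95 = 285, change +45.
- Control: 240, then 240, change 0.
- Difference in changes: 45, and 45/240 = 18.8%. The whole artefact survives.

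**4. How often this would reach significance.** Simulation with no true effect: 40 facilities per arm, 4,000 runs, two-sided 5% tests. Assumed: mean 300 events a year, between-facility CV 0.8, year-to-year CV 0.15, completeness changing in the intervention arm only.

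| Completeness | Apparent rise | Paired t-test, intervention arm | Between-arm t-test of changes |
|---|---|---|---|
| no change | 0 | 5% | 4% |
| 80% to 85% | 6% | 27% | 16% |
| 80% to 90% | 12.5% | 76% | 49% |
| 70% to 90% | 29% | >99% | 97% |

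**5. Common growth in volume.** Same set-up, completeness constant, equal volumes in the two arms. Growth of 5% or 10% in both arms makes the paired test significant in 19% or 57% of runs. The between-arm test stays at about 5% and 4%.

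**6. Unequal volumes.** With 10% growth in both arms and recorded baseline means of 480 and 240, the changes are 48 and 24. The difference is 24 events with no effect, while the ratio of ratios is 1.10/1.10 = 1. In simulation, the between-arm test of raw changes was falsely significant in 8% of runs at a 1.5-fold volume difference and 14% at 2-fold. On the log scale it stayed at about 5%. These volume ratios are assumed.

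**7. What a ratio can and cannot do.** Take 150 true fourth visits among 300 registrants.
- Both at 80%: 120/240 = 0.50. Both at 95%: 142.5/285 = 0.50. The artefact cancels.
- Numerator at 95%, denominator still at 80%: 142.5/240 = 0.594, again +18.8%. It does not cancel.

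**The case against.** - **Facility size.** A paired test compares each facility with itself, so fixed size cancels; with larger facilities and no growth, about 4% of runs were significant. This stands. What remains is growth over the year, unequal volumes in a comparison of raw changes, and the cross tabulation of raw counts.
- **Council populations.** A reader might infer a 2.8-fold volume difference, since the 2012 council populations sum to 3,885,429 (intervention) and 1,387,674 (control). The documents do not support that. Ten facilities are sampled per council, and nothing ties council population to the volume of a sampled facility.
- **Certainty and sign.** It is tempting to say that better reporting will inflate the counts. No completeness figure is given, and the article poses improvement in data quality as a question. Better accuracy could also correct over-reporting and lower the counts. Only 'can' is supportable.
- **Direction.** It would go too far to call every indicator uninterpretable. Deliveries, fourth visits and testing have an intended direction, and ARV coverage is already a proportion. The objection holds except for HIV-positives and maternal deaths.
- **Partial safeguards.** Data quality is measured as its own outcome, and Table 1 lists document review, questionnaires and interviews beside the DHIS2 form for health outcomes. The tools are in S2 File, which is not shown, so one cannot say that no register check is planned. But the article does not link the data-quality outcome to the reading of the health indicators.
- **Level of detail.** Count models and offsets are commonly left to an analysis plan. That is fair as to the model. The article, however, does fix the indicators and a test, and following them as written can mislead.

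**Conclusion.** The concern holds in this form: five of the six DHIS2 outcomes are counts, the named test is within-group over time, and their source is part of the system the initiative is meant to improve. A change in recording in the intervention arm can therefore be mistaken for a health effect, with or without the control arm.

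The size and sign are unknown. The 6, 12 and 19% rises rest on assumed completeness and no true change; the false-positive rates also rest on the assumed event volume and variability. For HIV-positive women and maternal deaths, a rise may reflect better detection or recording as well as worse health, and the count alone cannot separate them.

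The volume problem is secondary. It concerns growth over the year under the paired test, and unequal facility volumes if raw changes are compared between arms; the facility-level difference is not given. The outcomes and test should be changed before the end-line analysis.

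**What to change.** 1. Define the outcomes as ratios from the same DHIS2 extraction: fourth visits per ANC registrant, women tested per registrant, positives per woman tested, ARV per positive woman, and maternal deaths per facility delivery. Deliveries have no such denominator; analyse them on the log scale or with a count model.
2. In Table 2, row 4, replace the paired t-test with an arm-by-period comparison: a Poisson or negative binomial model with offset, or an analysis on the log scale, allowing for clustering within facility.
3. Report maternal deaths descriptively.
4. Report the data-quality outcome already planned by arm and period beside the health outcomes. State in advance that count changes will not be attributed to health effects where reporting changed differently by arm.

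The cost is a few more DHIS2 fields and slightly more analysis. Items 1 and 2 deal with growth and volume. They remove the recording bias only where numerator and denominator completeness change alike, and a log scale alone does not remove it for deliveries, so item 4 is needed as well.

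A check of DHIS2 against facility registers is optional. It is extra fieldwork and would detect errors in transfer to DHIS2, but not better recording at source, because the registers are also records that the initiative aims to improve.

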**Methods:**

We will conduct a hybrid type 2 effectiveness-implementation study employing a mixed method controlled before and after design to measure the effects of data use interventions while simultaneously understanding the implementation of those initiatives. The controlled before and after entails measurement of the effects of the interventions at baseline and end line in a matched intervention and control health facilities using structured questionnaire to health workers (n = 440) and existing patients (n = 422) while also extracting selected health outcome variable from routine data in all participating health facilities (n = 80). The mixed methods component entails measuring the implementation outcomes (adoption, acceptability, fidelity and maintenance) and their moderators entails the integration of both quantitative and qualitative data collection, analysis, and interpretation (i.e. mixed methods) approach by using a structured questionnaire to implementers (health workers and managers) (n = 400). Experiential dimensions of implementation processes and moderators will be explored using qualitative interviews. Guided by implementation research theories and frameworks, a theory of change (TOC) is developed first to guide the evaluation of implementation processes and effects of the interventions. Descriptive and inferential statistics will be employed to analyze quantitative data whereas thematic analysis approach will be employed for qualitative data.

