#### a. Study sites

The intervention districts will be selected purposively based on the fact that the data use interventions will be implemented. The control districts will be selected from two regions to match the intervention districts based on geographical location (urban vs. rural). The health facilities from the selected districts were selected based on the following criteria: a primary public health facility, providing services for more than a year. Hereunder the characteristics of the selected districts are described.

Kinondoni and Temeke are urban districts (Municipality) in the Dar es Salaam Region, the business capital of Tanzania Mainland. The census of 2012 showed that the population of Kinondoni was 1,775,049 whereas that of Temeke District is 1,368,881.

Chamwino and Dodoma City councils are districts in Dodoma Region, the administrative capital of the united republic of Tanzania. The census of 2012 showed that the population of Chamwino was 330,543, whereas that of Dodoma city council was 410,956.

Tanga city council and Korogwe are districts in the Tanga region, one of the important cities in the coastal zone of the country. The census of 2012 showed that the population of Korogwe was 56,282 whereas that of Tanga city council was 273,332.

Mwanza city council and Misungwi District council are districts in Mwanza region, one of the important cities in the Lake zone region of the country. The census of 2012 showed that the population of Mwanza city council was 706,453 whereas that of Misungwi was 351,607.

The eight councils represents a mixture of metropolitan (Temeke & Kinondoni), urban (Dodoma City council, Mwanza city council, Tanga city council) and rural district councils (Chamwino, Korogwe and Misungwi). The study areas are suitable of generating outcomes that could easily be transferable to other similar settings in the country.

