We will collect health facility level data to assess the overall situation of quality of care from a total of 80 health facilities (40 from intervention health facilities & 40 from control health facilities).From each of the selected health facilities we will collect quantitative data from at least five participants (the chairperson of the health facility governing committee, in charge of the health facility, data focal person , in charge of RMNCAH services and in charge of outpatient services) making a total of 400 participants. This sample is adequate to conduct robust inferential analyses related to the effects of the data use initiative. Moreover, taking p = 50% and applying Cochrane formula while also accounting for refusals and the fact that some health facilities (especially the dispensaries) may not all the five staff, an addition of 10% to the minimum sample will be added to reach 440 participants.Also, from the selected facilities exiting patients will be systematically selected after gender stratification following medical consultations. The exit interview with Client/patients will be approached after they have received the services and are ready to go home. Respondents eligible for interview include all exiting patients or relatives of patients (aged above 18 years). They will be sampled to ensure equal numbers of men and women are captured. The sample is calculated using the Cochran formula (1977) [32]; by taking 50% as a proportion of patients’ perception on quality of primary health care services) and a power of 80% allowing for an estimated error margin of 5%, the sample size obtained was 384 patients. To account for refusals, an additional 10% of the sample will be added (n = 38), making a total of 422 patients.

The qualitative samples and sample sizes for this component are as follows:

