We will use purposive sampling technique, to select at least 8 participants for in-depth interviews as a sub-sample of exit interview questionnaire (for exiting patients) from each district, i.e., 4 participants from dispensaries and four participants from health centers, thus making a total of 64 patients. Also, a total of 4 health care workers will purposively be selected for in-depth interview per council, i.e., 2 participants from dispensaries and 2 participants from health centers, thus making a total of 32 in-depth interviews. The exact number of interviews will be based on saturation of information that is the sample could even be smaller or increase depending on saturation. The interviews will explore the process and experiential dimension of quality of care and will complement evidence emerging from the quantitative analysis.

*Data collection tools and procedures*. To understand the data use situation including their determinants (governance, technical, behavioral and context) and existing initiatives and the indicators related to quality of care at the health facility, we will rely on facility assessment tool, interviews with clients and a structured questionnaire to health care workers and an observation checklist. The tools aim at getting a holistic picture on changes in quality of care and related health outcomes overtime as the initiative is implemented or as a result of changes in time. The tools are described here under and are found in S2 File.

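### Maternal deaths are listed as a raw facility count with no denominator and fall under a paired t-test that suits so rare a count poorly

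*Protocol article*

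**What the plan says.** Section 4 (Study components), Study component 1, Data collection tools and procedures, names six indicators to be extracted from DHIS2 as health outcomes. The list closes with "Proportion of pregnant women on ARV to prevent HIV transmission and Number of Maternal Deaths". Maternal deaths are given as a number, with no denominator. The number of facility deliveries is the first indicator on the same list.

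The facilities are primary level. Section 1a asks for "a primary public health facility, providing services for more than a year", and the qualitative sampling shows two tiers: "4 participants from dispensaries and four participants from health centers". Section 4 measures the outcomes before the programme and one year after it.

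Table 2, row 4 (the DHIS2 extraction form) sets the level as "Health facility level / District level" and lists descriptive statistics, cross tabulation and a paired t-test. The test is worded as in row 3, "Paired sample t test for comparing means between the baseline and end-line surveys", apart from a hyphen. No other inferential method appears in row 4.

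The number of units differs between places. Row 4 has "Health facilities (N = 40), Districts (N = 4". The sampling text has "a total of 80 health facilities (40 from intervention health facilities & 40 from control health facilities", and the abstract speaks of "extracting selected health outcome variable from routine data in all participating health facilities (n = 80". Section 1a names eight councils, four per arm.

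**The concern.** There are two difficulties.

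First, a raw count of deaths combines how many women deliver in a facility with how often one of them dies. The initiative is meant to improve services and may well change how many women use them. If it does, the count moves even when risk does not.

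Second, maternal death is likely to be rare at primary facilities within a year. A t-test on facility means then rests on a few events spread over many zeros and has little power.

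At stake is what the study would report. A non-significant change could be taken as evidence of no effect on maternal deaths. A change driven by delivery volume or chance could be taken as benefit or harm.

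**Working it through.** **Figures in the article.** It gives no expected deaths, delivery volume or power for any DHIS2 indicator, so there is no stated figure for this outcome to reproduce. The Cochran calculation (384, raised to 422) concerns exit patients only.

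**1. Denominator.** Expected deaths = deliveries × deaths per delivery. As an illustration, if deliveries rise by 20% and risk is unchanged, the expected count rises by 20% and looks like harm. If deliveries rise by 20% while risk falls by one sixth, 1.20 × 0.833 = 1.00 and a real improvement disappears. This step needs no assumption about how rare deaths are.

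**2. Expected counts.** From the article: 40 facilities per arm and one year. Assumed: a baseline window that is also one year, 10 to 60 deliveries per facility per month, and 20 to 100 deaths per 100,000 deliveries occurring at these facilities. With m deliveries per month and r deaths per 100,000, the mean per facility-year is μ = 12 × m × r / 100,000. The arm total is 40μ and the share of facilities with no death is exp(−μ).

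- Low end: μ = 12 × 10 × 20 / 100,000 = 0.024. Total 40 × 0.024 = 0.96. Share at zero exp(−0.024) = 98%.
- High end: μ = 12 × 60 × 100 / 100,000 = 0.72. Total 40 × 0.72 = 28.8. Share at zero exp(−0.72) = 49%.

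**3. Power if deaths are halved.** This was simulated with independent Poisson counts and a two-sided 5% level. The paired test uses the 40 intervention facilities. The between-arm test is a two-sample t-test on facility changes, 40 against 40. Row 4 does not state the second test, but it is what a controlled before-and-after claim needs.

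| Deliveries per month | Deaths per 100,000 | Deaths per arm-year | Facilities at zero | Paired, one arm | Between arms |
|---|---|---|---|---|---|
| 10 | 20 | 1.0 | 98% | 1% | 4% |
| 30 | 50 | 7.2 | 84% | 17% | 11% |
| 30 | 100 | 14.4 | 70% | 33% | 17% |
| 60 | 100 | 28.8 | 49% | 57% | 29% |
| 60 | 200 (outside the range) | 57.6 | 24% | 86% | 52% |

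Simulation error is about one percentage point.

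**4. Deaths needed.** For 80% power on a log-rate scale, with RR the end-line to baseline rate ratio in the intervention arm, the baseline deaths needed per arm are (1.960 + 0.842)² × (1 + 1/RR) / (ln RR)² for one arm before and after. For the controlled comparison, 1 + 1/RR becomes 3 + 1/RR. At RR = 0.5 the results are 7.85 × 3 / 0.480 = 49 and 7.85 × 5 / 0.480 = 82. Step 2 gives 1 to 29.

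**5. District level.** There are four councils per arm. With an assumed 20 deaths per council, power for a halving is about 68% paired and 51% between arms, and for a 30% reduction 30% and 23%. With an assumed 100 deaths per council, a 30% reduction gives 85% and 73%. These figures assume the same true rate change in every council, with no other variation between councils.

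**The case against.** The strongest reply is that maternal deaths are one of six indicators, not a declared primary outcome, and that no sample-size claim rests on them. Row 4 assigns methods to the whole form, already includes descriptive statistics, and does not say that each indicator will be t-tested. Section 5 also mentions regression, and models for single indicators may sit in a fuller document. This limits the importance of the point, and I accept it. It does not remove the point: the paired t-test is the only inferential method row 4 gives for this source, maternal deaths are not exempted, and the count has no denominator.

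A reader might go further and infer that the count sits at its floor, that it records where a woman died rather than whether mortality changed, and so that it cannot show an effect. The documents do not support this.

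- They give no counts, volumes or rates. At the top of the assumed range about half the facilities record a death in a year. If the rate did not change, only about 38% of before-after changes would be exactly zero.
- At 60 deliveries a month and 200 deaths per 100,000, the paired test has about 86% power for a halving.
- Nothing is said about referral or how deaths are attributed to a facility. Distortion by referral is possible, but it is conjecture here.

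District extraction is also a fair reply. Council counts are larger, and the initiative works partly at council level. However, there are only four units per arm, and council totals can include facilities outside the ten sampled in each council.

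**Conclusion.** The concern holds in a limited form. The lack of a denominator is plain from the text and matters whatever the death rate, because the count moves with another listed outcome. The weakness of the test depends on assumed volumes. Within 10 to 60 deliveries a month and 20 to 100 deaths per 100,000, power for a halving runs from about 1% to 57% (paired, one arm) and from 4% to 29% (between arms). The higher paired figures come from a test that ignores the controls, so they cannot support a claim of effect in a controlled design. The indicator is unlikely to show an effect at facility level under these assumptions, but at higher volumes or rates it could.

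**What to change.** In the DHIS2 indicator list (section 4, Study component 1) and in Table 2, row 4:

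- Take maternal deaths out of the t-tested indicators.
- Report arm totals at baseline and end line per facility deliveries, with exact Poisson intervals.
- State that no conclusion of effect or of no effect will be drawn from this indicator.
- Rest health-outcome conclusions on the more frequent indicators already extracted, such as facility deliveries, fourth antenatal visits and HIV testing.
- In the same edit, reconcile the 40 facilities and 4 districts of row 4 with the 80 facilities and eight councils elsewhere.

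This is a change of wording. The denominator is already on the extraction list, so no new data are needed. The cost is that the study gives up a formal test on maternal deaths. Dividing by deliveries would not settle how deaths after referral are counted, so the article should say how such deaths are attributed if that is known.
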